#### Listening effort

A listening effort test is applied using the same matrix as for sentence recognition. Participants are asked to rate the amount of effort involved in attempting to understand sentences in the presence of noise at different SNRs. During this procedure, as explained in more detail by Devocht et al. [54], sound is presented from a speaker and subjective rating is monitored on a touch screen using a 13-point scale ranging from no effort to extreme effort. The noise level is fixed at 65 dB SPL, while speech level is varied in order to create different SNRs according to the individual SRT of each participant, as determined in the corresponding listening condition during sentence intelligibility in noise. Overall, six levels were set below and above the participant’s individual SRT (SRT − 6, SRT − 3, SRT, SRT + 3, SRT + 6, SRT + 9).

#### Loudness scaling

ACALOS [48] will be performed to estimate the course of loudness perception between minimal audible level and maximum comfortable level with the CI and hearing aid alone. During this procedure, loudness levels are automatically adjusted to the participant’s individual auditory dynamic range without employing any pre-measurement. Participants will be presented with a one third octave band-noise from a speaker (center frequencies 250, 500, 1000, 2000, 4000 Hz) at different loudness levels (range 0–95 dB SPL with upper level depending on frequency), coming from a loudspeaker at the front (0°). After each stimulus, subjects are asked to rate loudness on an 11-point scale ranging from inaudible to too loud on a touch screen. As mentioned above, loudness scaling will be used to perform experimental HA fitting during phase 2.

#### Frequency selectivity

The spectral-temporally modulated ripple test (SMRT, available at www.ear-lab.org/smrt.html) will be used to measure the capability to spectrally resolve frequency information, which is known to be related to performance in understanding speech [55, 56]. This adaptive forced-choice test is used to measure the participant’s ability to discriminate stimuli that are modulated in the frequency domain [57]. During the test, participants are presented with two intervals: one contains a reference stimulus with 20 ripples per octave, the other contains the target stimulus, which has a varying ripple rate. The target stimulus initially has 0.5 ripples per octave, but is modified using a 1-up/1-down procedure with a step size of 0.2 ripples per octave, until the subject can no longer distinguish between reference and target stimulus [57]. Stimuli will be presented from a speaker and participants will be asked to select which stimulus is different. The test is completed after 10 reversals: thresholds are calculated as the average scores of the last 6 reversals. The average values of test-retest are recorded as outcome measures.

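### As described, the ripple test tracks 50% correct in a two-interval task where guessing also gives 50%, so its threshold has no defined performance level and is noisier than it need be

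*Protocol article*

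**What the plan says.** The section on frequency selectivity in the protocol article describes the ripple test (SMRT), which Table 2 lists as a secondary outcome. It fixes the following:

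- Task: "This adaptive forced-choice test is used to measure the participant’s ability to discriminate stimuli that are modulated in the frequency domain".
- Trial structure: "participants are presented with two intervals: one contains a reference stimulus with 20 ripples per octave, the other contains the target stimulus".
- Start, rule and step: "The target stimulus initially has 0.5 ripples per octave, but is modified using a 1-up/1-down procedure with a step size of 0.2 ripples per octave".
- Stated end of tracking: "until the subject can no longer distinguish between reference and target stimulus".
- Response: "participants will be asked to select which stimulus is different".
- Stop and threshold: "The test is completed after 10 reversals: thresholds are calculated as the average scores of the last 6 reversals".
- Outcome: "The average values of test-retest are recorded as outcome measures".

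No other part of the article gives a different number of intervals, a different rule or a target percent correct.

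**The concern.** An adaptive track measures something definable only if its rule settles at a percent correct that lies above guessing and below perfect performance. Here the rule and the number of intervals point to the same figure, which is chance. Above the listener's limit, correct and wrong answers are equally likely at every ripple rate, so nothing pulls the track back towards that limit.

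The response instruction is a second sign that the description does not hold together. Of two sounds, each differs from the other, so asking which one differs has no unique answer unless the listener already knows the reference.

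At stake is a within-person comparison of two maps in as few as 20 participants. Avoidable measurement noise costs precision there, and a threshold without a known performance level is hard to interpret or to set beside other work.

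**Working it through.** The article states no target percent correct for this test, so there is no figure to reproduce. The check has two parts.

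**1. Tracked point against chance (no assumptions needed)**

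Inputs from the frequency-selectivity section: forced choice, 2 intervals, 1-up/1-down.

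- A rule that moves harder after n correct answers and easier after one wrong answer balances where p^n = 0.5. With n = 1, p = 0.50.
- Chance with m intervals is 1/m. With m = 2, chance = 0.50.
- Detection at the tracked point, corrected for guessing: (p − chance)/(1 − chance) = (0.50 − 0.50)/(1 − 0.50) = 0.

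Two common alternatives, for comparison:

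- Three intervals, 1-up/1-down: (0.50 − 0.333)/(1 − 0.333) = 0.25.
- Two intervals, 2-down/1-up: p = √0.5 = 0.707, and (0.707 − 0.50)/(1 − 0.50) = 0.41.

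Both targets lie above chance.

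**2. Size, with the stated stopping rule (assumptions needed)**

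From the article: start 0.5, step 0.2, 10 reversals, mean of the last 6. Assumed, because the article gives no psychometric function: p(correct) = 1/m + (1 − 1/m) × logistic((midpoint − x)/scale), no lapses, midpoints 1, 2 and 4 ripples per octave, scales 0.1 to 0.8.

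Simulated threshold for a midpoint of 2, mean (SD):

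| Scale | As written | 3 intervals, 1-up/1-down | 2 intervals, 2-down/1-up | Variance ratio, vs 3 intervals | Variance ratio, vs 2-down/1-up |
|---|---|---|---|---|---|
| 0.2 | 2.60 (0.44) | 2.25 (0.24) | 2.09 (0.19) | 0.44²/0.24² = 3.4 | 0.44²/0.19² = 5.4 |
| 0.3 | 2.66 (0.47) | 2.30 (0.29) | 2.08 (0.24) | 0.47²/0.29² = 2.6 | 0.47²/0.24² = 3.8 |
| 0.4 | 2.71 (0.50) | 2.31 (0.34) | 2.06 (0.30) | 0.50²/0.34² = 2.2 | 0.50²/0.30² = 2.8 |
| 0.8 | 2.77 (0.65) | 2.28 (0.49) | 1.86 (0.43) | 0.65²/0.49² = 1.8 | 0.65²/0.43² = 2.3 |

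- *Low end of the ratios:* midpoint 4 at scale 0.8, 0.67²/0.54² = 1.5 and 0.67²/0.47² = 2.0.
- *High end:* scale 0.1, about 5 and up to about 11.
- *Upward shift from the assumed midpoint:* 2.60 − 2 = 0.60 at scale 0.2 and 2.77 − 2 = 0.77 at scale 0.8. Over all settings it runs from about 0.5 (scale 0.1) to about 0.9 (1.93 − 1 = 0.93 at midpoint 1, scale 0.8). The three-interval version also lies above the midpoint, but less: 2.25 − 2 = 0.25 at scale 0.2.
- *Response to ability at scale 0.3:* midpoints 1, 2 and 4 give 1.69, 2.67 and 4.67 as written. That is (4.67 − 1.69)/(4 − 1) = 0.99 per unit of true midpoint.

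**The case against.** The strongest reply is that the test still works as a measure. A reader might infer that the threshold is undefined, or that it reflects runs of lucky guesses rather than spectral resolution. The documents do not support that. The article stops the track at 10 reversals, and under that rule the value rises almost one-for-one with ability. The upward shift is similar across midpoints at a given slope, so much of it would cancel when two maps are compared in the same person. It grows as the assumed slope becomes shallower, so full cancellation needs similar slopes under both maps.

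Simulations with 60 or 200 reversals show the as-written track drifting upward and spreading. That illustrates the missing convergence point, but it is not a consequence for this trial, which does not run such tracks.

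Three further points stand in part:

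- **Size of the noise.** It depends on a slope that the article does not give, so no single multiple can be quoted. It is also per-track noise: averaging test and retest halves it if the two tracks are independent. The same averaging would halve it under the alternatives, so the ratios remain.
- **The response instruction.** The reference is always 20 ripples per octave, so a listener who has learned that sound can answer. The wording is awkward for two intervals but not impossible.
- **A reporting slip.** The article names a ready-made test and cites a source for the procedure, which is not at hand. The odd-one-out wording suggests that the paragraph may misdescribe the software. If so, the data carry no extra noise and only the text is wrong. The article alone cannot settle this, and nothing in it corrects the description.

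**Conclusion.** The point holds in a limited form. The described procedure is internally unsound: its tracked point equals guessing, so the staircase has no convergence point and the threshold no defined performance level. This follows from the stated number of intervals and the stated rule alone.

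Run as written, the outcome remains usable but shifted and noisier, by the ranges shown in the working. Those ranges assume a logistic psychometric function without lapses and scales from 0.8 to 0.1. Noise was higher than under either alternative at every setting tried.

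The reach is small. The ripple test is one of several secondary outcomes, listed at four time points. It enters neither the primary outcome nor the sample size, and hearing-aid fitting uses loudness scaling instead. What suffers is the precision and interpretability of this one comparison. Whether the fault lies in the test or only in its description is open.

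**What to change.** 1. Check which procedure the installed software runs.
2. If it presents three intervals (two references, one target, odd one out), correct the paragraph to say so. The cost is one sentence.
3. If it really presents two intervals, move to a rule whose target lies above chance. Either use three intervals with 1-up/1-down (50% correct against chance of 33%), or keep two intervals with 2-down/1-up (70.7% against 50%) and ask which interval holds the target.
4. In either case, state the percent correct tracked, and use one version for both maps within each participant and visit.
5. Analyse data collected under the earlier version separately, or flag them.

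Three intervals make each trial slightly longer. The 2-down/1-up rule needs about 60% more trials (44 against 27 at a midpoint of 2; 44/27 = 1.63). The larger cost is a possible version break. Recruitment began in March 2019 and the protocol version is dated January 2020, so testing has probably started, and a change now would put thresholds from different visits on different scales.

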#### Questionnaires

Participants will be asked to rate their satisfaction at every visit in a short questionnaire to determine their overall preference for either standard or experimental CI and hearing aid settings in everyday life. Satisfaction will be rated on a 10-point visual analogue scale on the subtopics of speech understanding, sound recognition and sound quality. Other questionnaires that will be administered include the Speech-Spatial-Qualities of Hearing Scale (SSQ-12) [58, 59], the Health Utility Index Mark 3 (HUI-3) [60], the translated [61] Icepop Capability measure for Adults questionnaire (ICECAP-O) [62] and a sound quality questionnaire by Devocht et al. [54] based on the descriptions of Boretzki [63].

### Compliance

In the first 3 months of the study, participants are required to wear their CI processors according to their personal randomization schedule. They should also wear their contralateral hearing aid for at least 50% of the CI wearing time over the course of the first 6 months, in order for the subject to be included for the experimental hearing aid fitting. Participants are asked to report the wearing time of both their CI processors and their hearing aid in daily diaries. By comparing these values to the ratios in the randomization schedule, differences in compliance will be calculated at regular intervals over each time window and compared to a set of cut-off points (see Additional file 1: research protocol). Since data logging features are not currently available in the CI research fitting software BEPS+, the only check on reliability of patient diary reporting is through the data logging of the hearing aid in Phonak Target. In the case of minor randomization deviations, participants will be treated as protocol deviators and will be removed from the per-protocol analysis population. In the case of severe non-compliance with randomization procedures, participants will be removed from the intention-to-treat analysis population.

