### Daily-randomization procedure

In this new type of trial design subjects act as their own control and treatment allocation is based on daily randomization. Two speech processors (physically labeled with either a green circle or a purple triangle) will be given to each participant, one of which will be programmed with the experimental settings and the other with the standard settings. Each day, subjects will be allocated to wear one of the two processors for a period of 3 months. A scheme with corresponding labels will be provided for each participant (Fig. 2). By equipping participants with two different processors, instead of one processor with FAT settings on different program slots, it is thought that issues with compliance are less likely to occur.

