Importantly, in our design, subjects will not be allocated to the same program for more than 2 days consecutively in the first time-window and no more than 4 days consecutively in the second time-window. The aim of this was to prevent the development of a fixed preference to any program that is given most during the first period of rehabilitation (i.e. either the experimental or standard program). Specifically, based on an analysis of clinical data within Maastricht UMC+ and published studies [32, 35] two distinct time periods have been roughly defined in the learning curve of patients with CI. The first 4 weeks of CI rehabilitation constitute the first time-window as they appear to be characterized by a large improvement in word recognition. Thus, this first period of adaptation can be considered crucial in the learning process. Therefore, a predominance of either the standard or experimental program during this time window will have a major impact on the preference for one or the other. CI rehabilitation tends to show a more flattened learning curve after 4 weeks (second time-window). Thus, by limiting the allocation to the same program to a maximum of 2 days consecutively in the crucial first 4 weeks, and no more than 4 days consecutively thereafter, we avoid the development of a fixed preference based on exposure time.

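### Compliance is scored on wearing-time ratios, which within a scoring interval cannot detect departures from the daily allocation or breaches of the run limits

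*Protocol article*

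**What the plan says.** The Daily-randomization procedure section of the protocol article makes the day the unit of allocation: "Each day, subjects will be allocated to wear one of the two processors for a period of 3 months". The same section limits how long one processor may be allocated without a break: 2 days in the first 4 weeks and 4 days after that. The Study design part of the Discussion repeats the limit ("subjects will not be allocated to the same program for more than 2 days consecutively in the first time-window") and gives the reason, which is to stop a fixed preference forming during early adaptation.

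The Compliance section sets the participant's duty for the first 3 months: "participants are required to wear their CI processors according to their personal randomization schedule". The data source is daily: "Participants are asked to report the wearing time of both their CI processors and their hearing aid in daily diaries". For objective verification, "the only check on reliability of patient diary reporting is through the data logging of the hearing aid in Phonak Target", so nothing independent records which implant processor was worn.

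The measure itself is "By comparing these values to the ratios in the randomization schedule, differences in compliance will be calculated at regular intervals over each time window". The resulting differences are set against cut-off points held in Additional file 1. Minor deviations remove a participant from the per-protocol population. In severe cases "participants will be removed from the intention-to-treat analysis population".

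**The concern.** What is randomised is the processor for each day. What is scored is the share of wearing time on each processor over an interval. The two agree for a participant who follows the schedule with equal daily hours, but they can diverge in both directions.

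- **Missed departures.** A participant can regroup days into longer runs and keep the scheduled share. Longer runs are what the 2-day and 4-day limits exist to prevent.
- **False flags.** A participant can wear the right processor every day but take one off earlier. The ratio shifts although the allocation was obeyed. If the shorter hours reflect dislike of that map, the flag is related to patient preference, which the assessment schedule (Table 2) lists among the primary outcomes.

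The score decides who is analysed. With 20 to 30 participants, each wrong inclusion or exclusion carries weight.

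**Working it through.** The plan gives no figure for this point to reproduce. The check is what a ratio can and cannot detect.

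**Inputs from the article:** one processor per day; run limit 2 days in weeks 1-4 and 4 days afterwards; diary wearing times compared with schedule ratios at regular intervals.
**Assumptions, not in the article:** 84 days, equal hours per day unless stated, no balancing beyond the run limits, tolerances of 10 or 20 percentage points for illustration.

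Let p be the scheduled share of one processor in an interval and q the worn share. The deviation is |q − p|. Neither term depends on the order of days.

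**Runs within an interval**
- *14 days, scheduled 7:7.* Two 7-day runs: |7/14 − 7/14| = 0. Scheduled 8:6: |7/14 − 8/14| = 7.1 points. In 20,000 simulated schedules, the split was 7:7 in 43% (days 1-14) and 25% (days 29-42). It was no further from balance than 8:6 in 92% and 68%.
- *7 days, scheduled 4:3.* A 4-day run then a 3-day run: deviation 0, against a limit of 2 in weeks 1-4. Runs can also join across intervals: 4 days A and 3 days B, then 3 days B and 4 days A, gives 6 consecutive days on B with deviation 0 in both weeks.
- *What the ratio does catch.* With a limit of 2, one processor can be scheduled on at most 5 of 7 or 10 of 14 days, which is 71% either way. Wearing one processor throughout such an interval deviates by at least 100 − 71 = 29 points.

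**Daily reversal.** Here q = 1 − p, so the deviation is |2p − 1|. It is 0 only if p = 1/2. In a 7-day interval the minimum is |2 × 4/7 − 1| = 14 points.

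**Simulated patterns if the ratio is taken once per window**

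| Pattern | Day agreement | Weeks 1-4 (28 days) | Weeks 5-12 (56 days) |
|---|---|---|---|
| Scheduled counts in two blocks | about 50% | deviation 0; mean longest run about 15 days | deviation 0; mean longest run about 30 days |
| Coin toss each day | about 50% | within 10 points 61%, within 20 points 94.5% | 75%, 98.5% |
| Strict alternation | 50% | within 10 points 97% | 94% |
| Daily reversal | 0% | exactly 0 in 34%, within 10 points 81% | 14%, 61% |

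**The opposite error.** With a 1:1 schedule followed on every day, let hours on one map be a fraction r of hours on the other. Its share is r/(1 + r). A 10-point deviation needs r/(1 + r) = 0.40, so r = 2/3. A participant wearing one map two-thirds as long each day has 100% day agreement and a 10-point deviation.

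**The case against.** The strongest reply is that the article only summarises the rule. Additional file 1 holds the cut-offs, probably the interval length, and possibly a day-level check. The removal triggers are worded as deviations from, or non-compliance with, the randomisation and do not mention a ratio alone. This limits what can be said about how many departures escape. It does not rescue the stated measure: the article cites the file for thresholds on the calculated differences, and no threshold makes a ratio sensitive to order.

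Second, scoring at regular intervals bounds the problem. That is right. A 14-day run filling an interval would show clearly, and a reader who infers that two 14-day blocks would count as perfect compliance is assuming a single 28-day interval, which the article does not state. Shorter intervals still leave order within each one, and joins between them, unchecked.

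Third, the Discussion argues that total exposure matters more than its distribution, and it fears predominance of one program. A ratio tracks both, so it deserves to stay. The exposure argument, however, is made about differences between randomisation schemes, and the same Discussion imposes run limits because consecutive days are thought to matter.

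Fourth, day agreement is not free of selection. A participant who swaps out a disliked map fails it too, and one who wears that map only briefly on its assigned days may pass if it is still the one mainly worn. This stands, and is a reason to use the measures together.

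**Conclusion.** The point holds in a limited form. As stated, the compliance measure is blind to order within each scoring interval. A participant can depart from the daily allocation and exceed the run limits with little or no deviation, and a participant who obeys every assignment can be flagged for shorter hours on one map. The first part follows from the definition of a ratio and needs no simulation. The simulated percentages depend on the listed assumptions and on the interval length.

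Two stronger readings are tempting but unsupported. One is that a participant who reverses the schedule every day would count as fully compliant. That is exact only in a balanced interval; otherwise it depends on cut-offs that are not shown. Reversal also keeps the run lengths unchanged, so it does not breach the limits. The other is that the primary comparison is thereby invalid. The sample-size section places word recognition at 6 months, after the free-choice period, and ties it to no particular day's allocation.

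Removing participants from the intention-to-treat population for non-compliance is a separate weakness that would exist under any measure. It belongs here because it makes a misclassification more costly.

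**What to change.** Define compliance in the analysis plan from the existing daily diaries, with three measures per time window:

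1. the proportion of days on which the assigned processor was the one mainly worn;
2. the longest run of days on one processor, compared with the limits already in the protocol;
3. the wearing-time ratio against the schedule, kept as a complementary measure of exposure.

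If Additional file 1 already contains a day-level or run-length check, state it in the definition. Use the measures only to define the per-protocol set. Delete the rule that takes severely non-compliant participants out of the intention-to-treat population.

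The cost is wording and slightly more analysis work; no new data are needed. Per-protocol exclusion may still be partly related to outcome, and the diary remains without objective verification for the implant processors, so the per-protocol result should be read as supportive.

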#### CI frequency mapping

The calculated frequency distribution is used to create the experimental frequency allocation table (FAT), which pursues individualized tonotopical alignment. In this setting, the Advanced Bionics Phantom functionality is enabled [41], which delivers low-frequency information beyond the most apical electrode of the array by operating as a virtual channel created using partial bipolar stimulation [41–43]. By adding a low-frequency channel, the Phantom feature reduces the gap between the actual and tonotopical place of low-frequency stimulation and at the same time increases the number of channels that can be tonotopically matched for the remainder of the array. For details on Phantom stimulation, see Nogueira et al. [42].

The imaging-based frequency-to-place distribution and the Phantom feature are applied to create the experimental FAT by overlapping the tonotopical frequency distribution with its corresponding electrode channels (Table 1). Ideally, this setting should be constructed as such that each position in the cochlea should merely be innervated by frequency inputs that align with its tonotopy. However, full tonotopical alignment is not always appropriate, as there are electrode contacts that fall out of the 250–8000 Hz frequency range that is covered by a CI processor. Due to shallow insertions or irregular lateral wall lengths, it is also possible that the most apical electrodes reach a tonotopical alignment that falls right within the speech spectrum. Leaving out all acoustic input below this point is expected to be detrimental for overall hearing performance. To address these issues, a set of rules will be applied as follows: (1) at least two channels (including Phantom) have to stimulate 1000 Hz or lower, (2) at least four channels have to stimulate 2000 Hz or lower, (3) at least seven channels have to stimulate 4000 Hz or lower and (4) the most basal channel has to be stimulated by 8598 Hz or lower. Participants will be excluded from study participation when it is not possible to assign a minimum of 8 channels [44] within the CI frequency spectrum while applying the rules stated above. This will be monitored throughout the study, with excluded participants taken out of the study and being transferred to standard clinical follow up.

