### Statistical methods, data reporting and analysis

The outline of this study can be categorized in multiple phases, each concerning different statistical outcomes, listening conditions and endpoints. The statistical analysis plan will be finalized before the database lock. In general, analyses will be carried out for each treatment option (experimental fitting versus standard fitting for both CI and hearing aid), for different outcomes (e.g. word recognition, subject preference, quality of life) and different listening conditions (with CI, hearing aid or bimodal). The main statistical analysis will focus on the question of whether the experimental fitting, based on individual imaging and tonotopical fit, will give rise to improved outcomes in word recognition compared to the standard fitting. Learning curves will be analyzed by calculating steepness and area under the curve. Normality will be assessed by examining histograms, Q-Q plots, and performing the Shapiro-Wilk test. Depending on whether normality can be established, either nonparametric or parametric statistical comparison tests will be performed. Analysis will be performed in all participants in the intention-to-treat population with separate reporting of participants who are included on a per-protocol basis. Results of these different outcomes will be presented as mean, standard deviation and percentile distribution. In the case of non-parametric testing, results will also be presented as median and interquartile range.

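### The population labelled intention-to-treat drops severe non-compliers, so the main analysis uses a compliance-filtered set and no analysis of everyone randomised is described

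*Protocol article*

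**What the plan says.** The Compliance section of the protocol article sets two levels of exclusion. For the lesser level: "In the case of minor randomization deviations, participants will be treated as protocol deviators and will be removed from the per-protocol analysis population". For the greater: "In the case of severe non-compliance with randomization procedures, participants will be removed from the intention-to-treat analysis population".

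The behaviour being judged occurs after randomisation: "In the first 3 months of the study, participants are required to wear their CI processors according to their personal randomization schedule". It is measured by self-report: "Participants are asked to report the wearing time of both their CI processors and their hearing aid in daily diaries". The diary times are set against the ratios in the schedule and "compared to a set of cut-off points (see Additional file 1: research protocol". The section adds that the research fitting software has no data logging for the implant processors, so the hearing aid's own log is the only check on the diaries.

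The statistical methods section then fixes the main population: "Analysis will be performed in all participants in the intention-to-treat population with separate reporting of participants who are included on a per-protocol basis". The article describes no other analysis set.

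**The concern.** An intention-to-treat set is defined by allocation and keeps participants whatever they later do. Here membership depends on adherence during the three months of daily-randomised wear. The two named populations therefore differ in how strict the compliance filter is, and neither is free of one.

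In this design, departing from the schedule usually means wearing one processor more, and the other less, than allocated. A participant who tolerates one map badly, or hears worse with it, could be more likely to depart. The article itself expects preferences to form: the Daily-randomization procedure section restricts the sequence to prevent them, and Table 2 lists preference among the primary outcomes. If non-compliance is related to the within-person map difference, removing non-compliers selects participants on a correlate of the quantity being estimated. The estimate would then be biased under a label that tells readers it is protected against this. With 20 to 30 participants, a few removals matter.

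**Working it through.** **1. Reproducing the plan's own figure.** The Sample size section gives N = 2 + (z₁₋α/₂ + z₁₋β)²/d². Solving for d gives d = (z₁₋α/₂ + z₁₋β)/√(N − 2). With α = 0.05 and power 0.80, the numerator is 1.960 + 0.842 = 2.802.
- N = 20: 2.802/√18 = 0.66, as stated.
- N = 30: 2.802/√28 = 0.53, as stated.

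The printed power of 0.08 does not reproduce these values (it gives 0.13 and 0.10); 0.80 does. That is a separate matter and does not affect this point.

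**2. Removal unrelated to outcome.** There is no bias, only a smaller N. Exact paired-t power (noncentral t, two-sided α = 0.05):

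| Removed | N from 20 | Power at d = 0.66 | N from 30 | Power at d = 0.53 |
|---|---|---|---|---|
| 0 | 20 | 80% | 30 | 80% |
| 1 | 19 | 78% | 29 | 79% |
| 2 | 18 | 75% | 28 | 77% |
| 3 | 17 | 72% | 27 | 76% |

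**3. Removal related to outcome.** The documents give neither the number of severe non-compliers nor any dependence, so everything in this step is assumed:
- N = 20 and no true effect.
- Paired differences are standard normal.
- A latent compliance score has correlation ρ with the difference.
- The k participants with the lowest scores are removed, so all removals come from one tail.

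Bias = −ρ × (sum of the k lowest expected normal order statistics)/(N − k). For N = 20 the three lowest are −1.867, −1.408 and −1.131. With ρ = 1:
- k = 1: 1.867/19 = 0.10 SD
- k = 2: 3.275/18 = 0.18 SD
- k = 3: 4.406/17 = 0.26 SD

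Smaller ρ multiplies these by ρ. Type I error was simulated with 400,000 samples per cell, using a one-sample t test on the retained differences:

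| ρ | Bias in SD, k = 1 / 2 / 3 | Two-sided type I error, k = 1 / 2 / 3 |
|---|---|---|
| 0 | 0 / 0 / 0 | 5% / 5% / 5% |
| 0.3 | 0.03 / 0.05 / 0.08 | 5.3% / 5.8% / 6.3% |
| 0.5 | 0.05 / 0.09 / 0.13 | 5.8% / 7.1% / 8.9% |
| 0.7 | 0.07 / 0.13 / 0.18 | 6.8% / 9.6% / 13.4% |
| 1 | 0.10 / 0.18 / 0.26 | 8.8% / 16.1% / 26.3% |

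The bias is proportional to ρ; the excess type I error is not. For k = 3 the excess over 5% is 21.3 percentage points at ρ = 1. Proportional scaling to ρ = 0.3 would predict 6.4 points of excess, or about 11%, whereas the simulated value is 6.3%.

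At N = 30 with k = 3, type I error is 6.0%, 8.3% and 11.9% at ρ = 0.3, 0.5 and 0.7.

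**The case against.** **The dependence is not documented.** A reader might infer that severe non-compliers are those who cannot tolerate one map, and that the main analysis is therefore biased in a known direction. The documents do not say this. Forgetting, or picking up the wrong processor, would also count as non-compliance. Participants are blinded, and the maps are reassigned at random to the two labels at each fitting, so a habit for one label does not become lasting exposure to one map. Runs on one processor are capped at two days, later four. After three months choice is free, so a preference can be acted on without breaching the schedule, and the endpoint used for sample size is at six months. These features weaken the link but do not remove it, because participants can still hear the maps. The Discussion reports a mean pilot shift of 1.36 octaves between them.

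**Each participant is their own control.** Removal deletes both conditions together, so arms are not unbalanced. That is correct. But the target is the mean within-person difference, and selecting people on a correlate of that difference biases it. If removals fall evenly in both tails, the mean does not shift.

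**The cut-offs are elsewhere.** Additional file 1 may define severe so narrowly that few are removed. That limits the size of the problem. It does not change the rule, which the article fixes itself: no cut-off makes a compliance-filtered set an intention-to-treat set.

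**Two further readings go too far.** One is that the plan has two per-protocol sets. Minor deviators stay in the main set, so it is better described as modified intention-to-treat. The other is that the eight-channel rule in CI frequency mapping is a second filter of the same kind, since the article says "This will be monitored throughout the study, with excluded participants taken out of the study". That rule concerns whether enough channels can be assigned from the imaging. Table 2 places the scan three weeks before activation, so the first assignment can precede any wear. Later exclusion remains possible, but on a technical criterion and not on wearing behaviour.

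**Conclusion.** The point holds as a mislabelled main analysis set. "Analysis will be performed in all participants in the intention-to-treat population" cannot mean all randomised participants while the Compliance section removes some of them for how they wore the devices. The exclusion rests largely on unverified self-report: a participant without a hearing aid has no logged check at all.

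The consequence for the result is conditional. With 20 participants and 1 to 3 removed from one tail, type I error is about 5% to 6% at a correlation of 0.3 and 7% to 13% at 0.7. It reaches 9% to 26% only if non-compliance ranks participants perfectly by their map difference, which is an extreme bound and not an expectation. The bias at 0.7 is at most 0.18 SD, against a stated detectable effect of 0.66 SD. The estimate shifts away from whichever map is avoided by those removed, and the documents do not indicate which that would be. Without any dependence, the cost is up to 8 percentage points of power with three removed at N = 20.

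**What to change.** - Define the intention-to-treat population as every participant issued a daily-randomisation schedule, analysed by programmed map with all collected CNC scores, whatever the wear compliance.
- Use the compliance cut-offs in Additional file 1 only for the per-protocol set. If the present filtered set is still wanted, report it as a named sensitivity analysis under its own label.
- Keep testing both maps in participants who deviate from the schedule, so that their outcomes exist for the main analysis.

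This is a change of wording in the protocol and the statistical analysis plan. The article says that plan will be finalised before database lock and that recruitment was still open at submission. No new measurement is needed provided deviating participants continue their test visits. The price is some dilution of the estimate, because a few participants will have had little practice with one map. The per-protocol analysis still shows the result in those who adhered.
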